**Table d35e730:** 

Measured outcome	Time window
Percentage of patients admitted to hospital	Within 14 days of alert
Percentage requiring any critical care admission	During index admission
Other key events (see below)	During index admission
Percentage discharged to institutional care	After index admission
All-cause mortality	At 90, 182 and 365 days
Renal function (eGFR)	At 90, 182 and 365 days

In a pragmatic study, patients will not be recalled for renal function testing; at the time points above, we will use the last observation carried forward for all living patients. Key events are these events as given in the discharge letter:
Cause of AKI: new glomerulonephritis or new urinary obstruction diagnosis.Complication of AKI not requiring dialysis: new pulmonary oedema, uraemia ≥30 mmol/L or hyperkalaemia (≥6.0 mmol/L).

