## Background and rationale

Acute kidney injury (AKI) is a common condition. Its prevalence in UK is estimated to be >20% of emergency admissions.^1^ Worldwide incidence is about 21.6% in adults in hospital settings, as shown in a recent meta-analysis.^2^ Mortality due to AKI is high. Recent studies show an overall mortality of >23% in the UK,^3^ and a similar percentage worldwide.^2^ There are recognised deficiencies in the clinical care of patients with AKI.^4^ The UK's National Confidential Enquiry into Patient Outcome and Death (NCEPOD)^4^ showed that 14% of fatal AKI cases were avoidable. One large UK study found that mortality in patients with AKI was significantly higher in the 55% of acute trusts that did not have onsite renal teams.^5^ AKI aetiology is diverse, and it usually occurs in the setting of other comorbidities. However, few studies have looked into the effect of non-renal comorbidities on outcome. Charlson comorbidities have been used to predict outcome in end-stage renal disease.^6–8^ Our previous work examined the role of comorbidity in AKI, demonstrating the impact of solid and haematological malignancies, as well as the total burden of non-malignant comorbidities.^9^ Intensive care patients with AKI and uncontrolled malignancy are known to have poor outcome.^10^

Advances in technology show promise in the early identification of AKI, using electronic alerts.^9^
^11^ Theoretically, bringing the recent rise in creatinine to clinicians' attention should prompt improvements in management. However, a recent study using alerts alone failed to demonstrate any improvements in outcome.^12^

The concept of an Outreach team has been established in critical care for many years, offering rapid assessment to deteriorating patients. One large cluster randomised trial (CRT) failed to show a significant impact of Medical Emergency Team in reducing hospital cardiac arrests.^13^ In the UK, the introduction of critical care Outreach in an 800-bed general hospital significantly reduced mortality.^14^ Two large meta-analyses were conducted analysing trials of rapid response teams (RRTs). Outreach teams were successful in reducing non-intensive care unit cardiac arrest by 34%, but mortality was not significantly reduced.^15^ Overcoming the barriers to implementation of the RRT service would further improve outcome.^16^ The dissociation between decline of cardiac arrest rates and mortality is not fully understood.

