### Quantitative analysis of clinical data

#### Estimates for the CRT

The main aim of this study is to test feasibility of the intervention and all study procedures. In addition, this pilot study will allow estimates of the uncertainty of the primary outcome (deterioration or death) to be used in planning a cluster trial. Secondarily, data from this study can be used to assess the prognostic model previously introduced. In addition, simple analyses will be conducted to look at CKD progression or development of end-stage renal disease as a result of AKI episode, and survival to discharge to a more dependent setting than at admission.

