### Outcomes

The primary purpose of this study is to assess feasibility and inform a full cluster randomised study. The primary outcome for the full study, also collected in this study, is reflected in the trial acronym: deterioration or death of the patient with AKI, and is a combination of:
All-cause death within 30 days;Any need for dialysis or renal replacement therapy (intermittent haemodialysis (typically at the Renal Unit of Birmingham Heartlands Hospital) or continuous renal replacement therapy (typically in the intensive care units of the Trust)) within 30 days;Progression of AKI stage without dialysis within 30 days after the alert (stage progression is stage 1 deteriorating to 2 or 3; stage 2 deteriorating to stage 3).

These were chosen to reflect the major, potentially modifiable, outcomes of concern for patients (death and/or dialysis) and renal units or hospitals (death, dialysis or deterioration). Stage progression (compared to non-progression) is known to be associated with increased mortality and length of stay in a multivariate analysis,^34^ and is a useful surrogate end point.

Secondary outcomes for the main study, collected to assess feasibility here, are as follows:

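### The institutional-care outcome takes no account of residence at admission, is not reconciled with the planned change-in-setting analysis, and could rise simply because frail patients survive

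*Protocol article*

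**What the plan says.** In the Protocol article, the table under Outcomes lists "Percentage discharged to institutional care" with the time window "After index admission". The row gives no denominator, does not mention residence at admission, and gives no rule for patients who die before discharge. It is introduced by the line "Secondary outcomes for the main study, collected to assess feasibility here, are as follows", so it is meant to carry over to the cluster trial.

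The section headed Estimates for the CRT names, among some simple additional analyses, "survival to discharge to a more dependent setting than at admission". That measure compares the discharge setting with the setting the patient came from. No sentence links it to the table row.

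Death is reported elsewhere. The primary composite includes "All-cause death within 30 days", and all-cause mortality has its own row, "At 90, 182 and 365 days". For renal function the article does say who is included ("we will use the last observation carried forward for all living patients"). It says nothing comparable for discharge destination.

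**The concern.** Two features of the row make a before–after difference hard to interpret.

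First, it records where patients went, not whether their situation changed. A care-home resident who recovers and returns to the same home is an event in the table row and not an event in the change-in-setting analysis. The key-events list directly below the table uses the qualifier *new* for diagnoses and complications that must be incident. The institutional-care row has no such qualifier, so its natural reading includes existing residents.

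Second, a patient who dies in hospital cannot have the event. Outreach aims to reduce death. If it succeeds among frail patients, some of them will leave hospital for institutional care, and the percentage can go up although no patient has done worse. The plan compares before with after within each site, so the row could move in the unfavourable direction because of a benefit. A main trial that took over this wording would face the same problem with more precision.

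**Working it through.** The article states no figure for this outcome, so there is nothing of its own to reproduce. The check concerns direction, followed by a range on assumed inputs.

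**1. The two measures side by side**

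| Patient | Table row | Change-in-setting analysis |
|---|---|---|
| Care-home resident, returns to the same home | event | no event |
| Lived at home, discharged to a care home | event | event |
| Died in hospital | cannot be an event | cannot be an event |

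The measures differ for existing residents. Both can be met only by patients who leave hospital alive.

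**2. Direction when survival improves**

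Let d be the share of admitted patients who die before discharge, i the share of survivors discharged to care, s the extra survivors as a share of all admitted, and f the share of those extra survivors discharged to care. Destinations of the original survivors are held fixed.

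- Survivors as denominator: i becomes [(1 − d)i + s·f] / (1 − d + s). This rises only if f > i.
- All admitted as denominator: (1 − d)i becomes (1 − d)i + s·f. This rises for any f > 0.
- Death or care, all admitted: d + (1 − d)i changes by −s(1 − f). This falls, or is unchanged if f = 1.

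**3. Illustrations (all inputs assumed)**

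d = 23% is a placeholder taken from the background statement "Recent studies show an overall mortality of >23% in the UK"; it is not a trial assumption about in-hospital death. The values of i, s and f have no source in the document.

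| i | s | f | Among survivors | Among all admitted | Death or care |
|---|---|---|---|---|---|
| 10% | 3 points | 50% | 10.0% → (7.7 + 1.5)/80 = 11.5% | 7.7% → 9.2% | 30.7% → 29.2% |
| 10% | 5 points | 60% | 10.0% → (7.7 + 3.0)/82 = 13.0% | 7.7% → 10.7% | 30.7% → 28.7% |
| 20% | 5 points | 10% | 20.0% → (15.4 + 0.5)/82 = 19.4% | 15.4% → 15.9% | 38.4% → 33.9% |

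The third line has f below i: the survivor percentage then falls, so a rise is not automatic. Over d 20–25%, i 5–20%, s 2–5 points and f 30–100% (f above i throughout), the survivor percentage rises by about 0.2 to 5.9 points.

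**4. Existing residents**

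Assume that 5% of survivors already lived in care and returned there, and that 5% of the other survivors are newly placed. The row then reads 5 + 95 × 0.05 = 9.75% of survivors. With d = 23% and 2 extra survivors per 100 admitted, all existing residents, it becomes (7.51 + 2)/79 = 12.0%. With 5 extra it becomes (7.51 + 5)/82 = 15.3%. New placement among those not previously in care stays at 5.0%. Taking 5–10% for both inputs, the row rises by about 2 to 5.5 points.

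**5. Is the change-in-setting wording enough by itself?**

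Same inputs, but the 2 extra survivors were not residents and half are newly placed. New placement goes from 3.66/77 = 4.8% to 4.66/79 = 5.9% of survivors, so the survival effect remains. Shown as three states per 100 admitted, the same change reads: died in hospital 23.0 → 21.0; more dependent setting 3.7 → 4.7; same or less dependent setting 73.3 → 74.3. The benefit is then visible.

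**The case against.** A reader might infer four stronger things that the article does not support.

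- *That it gives two conflicting definitions of one outcome.* It does not. The change-in-setting measure is named as a simple analysis, and a crude destination percentage can stand beside it. What is missing is a statement of how they relate.
- *That the percentage is taken among survivors and deliberately includes residents.* The denominator is unstated; only the numerator is necessarily limited to patients discharged alive. Inclusion of residents follows from a missing qualifier, and a fuller protocol or analysis plan may settle it.
- *That saving frail patients would be read as harm.* It could be, not would be. With survivors as denominator a rise needs f > i. Mortality at 30 days and later is reported alongside. The Statistical analysis section names dialysis use and non-dialytic complications as its safety indicators, not this row, and says the pilot lacks the power for a full before–after comparison.
- *That in-hospital mortality of 23% is expected here.* That figure is background from other studies. This study also recruits in primary care and excludes patients near the end of life.

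It is also fair that a stable share of existing residents affects the level in both phases and cancels in the difference. The article gives no shares. It accepts that more recurrent AKI patients may enter the before phase, but does not connect this with residence.

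These objections limit the size and certainty of the point. They do not remove it: the row as printed is absolute, the analysis planned elsewhere is relative, and neither shows in-hospital death beside placement.

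**Conclusion.** The point holds as a minor one. The table row and the change-in-setting analysis measure different things and should be reconciled. Taken literally, the row counts residents who return to their care home, and it can rise when frail patients survive, under the conditions on f given above.

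No trial figure changes, and the size cannot be derived from the document. The 0.2 to 5.9 points for the survival effect and the roughly 2 to 5.5 points for existing residents depend entirely on assumed inputs. The direction depends only on those conditions and on the original survivors' destinations being unchanged. No decision in the pilot rests on this row. It deserves attention because the article presents these outcomes as those of the main trial.

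**What to change.** Define the outcome in the table relative to the setting at admission, and say that this is the measure meant in the section on estimates for the CRT. Report it over all patients with an index admission as three mutually exclusive states:

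1. died in hospital;
2. left hospital alive for a setting of greater dependency than the one they came from;
3. left hospital alive for a setting of the same or lesser dependency.

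Adopting the change-in-setting wording without the first state would deal with existing residents but not with the survival effect. The crude percentage to institutional care may stay as a descriptive figure, with its denominator stated.

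The cost is one changed table row and the use of setting at admission, which the planned change-in-setting analysis already needs.

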## Methods

### Overall study design

We will run a quasi-experimental trial of a complex multifactorial intervention.^23^ Using a before and after study design, we will pilot the Outreach service to patients with AKI. Patients will be recruited once they have an electronic alert indicating that they have AKI. Inclusion and exclusion criteria will then be applied (box 1). There will be no patient-level randomisation to avoid the risk of contamination, as this is a pilot for a CRT. The study has been approved by (1) the National Research Ethics Service (Reference: 14/EM/0184, NRES Committee East Midlands—Nottingham 1, approved 22 May 2014) and (2) the Confidentiality Advisory Group (CAG Reference: CAG 2-07(a)/2014—approved 30 May 2014).
Box 1Inclusion and exclusion criteria for the Acute Kidney Outreach to Reduce Deterioration and Death (AKORDD) studyInclusion criteria:Adult (≥18 years) patients with an alert due to AKI from a blood test arising from Heartlands or Good Hope Hospitals (and their associated postcodes for outpatients/primary care).AKI stage 1, 2 or 3.Exclusion criteria:Patient deceased at the time of Outreach team intervention.Patient already accepted for dialysis by HEFT renal unit.Known dialysis/end-stage renal disease patients (excluded from alerts).Other patients with stable chronic kidney disease (definition of stable CKD), or progressive CKD where there is no obvious change in the rate of progression of the CKD (ie, no acute deterioration, just steady progression).Patients with CKD and stage 1 AKI based on an absolute creatinine rise of ≥26 µmol/L but who have a relative rise of ≤15% in creatinine are regarded as stable CKD and therefore not eligible for the study.Children or young people <18 years of age.Patients in the terminal phase of malignancy or end-stage major organ disease where they have little potential to benefit from Outreach. These would typically be identified as having a life expectancy likely to be <3 months.Patients lacking mental capacity (unless enrolment agreed in writing with a personal consultee or nominated consultee (after phase) or personal consultee (before phase)).Other technical aspects of making alert not credible: inadequate data; suppressed creatinine at baseline.

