### Intervention package

The Outreach team will advise on an evidence-based package of care (these interventions are limited to the intervention arm):
*Diagnostic and monitoring recommendations*—to rapidly establish a credible diagnosis of the cause of AKI including:
Improved assessment of volume status;Standardised use of urine dipstick (often missed);Appropriate sepsis investigations;Urgent ultrasound with suspected obstruction, while avoiding early ultrasound in patients at low risk of obstruction.*AKI treatment recommendations*—to treat correctable causes of AKI:
Rapid, limited treatment of hypovolaemia, with avoidance of iatrogenic fluid overload, recently recognised as a significant cause of mortality in AKI;Rapid sepsis therapy;Cessation of potentially nephrotoxic agents (many well known, such as ACE inhibitors and non-steroidal drugs, but others less well known such as Aciclovir);Urgent relief of urinary tract obstruction.*Recommendations to manage the acute illness:*
Where needed, recommendations will be made to address key aspects of the major underlying comorbidity;Improve nutrition, as malnutrition is known to be associated with poor outcome. Dietetic referral will be made for all appropriate inpatients with stage 3 AKI.*Pathway recommendations:*
For inpatients, refer to the Renal and/or Critical Care Outreach teams, as appropriate;For patients in the community, arrange urgent or immediate outpatient review or admission, as appropriate;Arrange formal palliative care when necessary.*Stage-based AKI management:*
Stage 1 patients will typically receive a single intervention call;Stage 2 patients will usually receive a single intervention call and be discussed with the renal consultant;Stage 3 inpatients will be reviewed by a consultant, ideally within 24 hours of the AKI Outreach team being aware of their presence in the intervention hospital (Heartlands Hospital);Rapid AKI follow-up clinic—we will offer surviving patients with stage 3 AKI a rapid follow-up clinic appointment, ideally within 7 days of discharge, or within 7 days of the alert if the patient is not admitted to hospital.

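### Unrestricted last observation carried forward for eGFR lets a creatinine from the AKI episode stand as kidney function at 90, 182 and 365 days (moderate; secondary outcome)

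*Protocol article*

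**What the plan says.** The secondary outcomes table in the Outcomes section of the protocol article lists "Renal function (eGFR)" at 90, 182 and 365 days. The text below it says that "patients will not be recalled for renal function testing" and that "at the time points above, we will use the last observation carried forward for all living patients". It gives no window around the time points, no minimum interval from the alert, and no exclusion of values from the index episode.

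Three other parts of the article bear on this:

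- **Entry.** Under Overall study design, "Patients will be recruited once they have an electronic alert indicating that they have AKI". The Alerts section explains that an alert comes from comparing the current creatinine with an earlier baseline.
- **Use of the data.** Under Estimates for the CRT, "simple analyses will be conducted to look at CKD progression or development of end-stage renal disease". The Statistical analysis section adds eGFR and CKD stage by group, and change within individual patients.
- **Follow-up.** Under Intervention package, "we will offer surviving patients with stage 3 AKI a rapid follow-up clinic appointment, ideally within 7 days of discharge", and "these interventions are limited to the intervention arm".

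**The concern.** Carrying a value forward presumes that little changes after it was taken. These patients are selected at an acute and often reversible departure from their baseline, so the presumption fails in the patients for whom the rule matters most: those with no later test. A creatinine from the episode can become the one-year eGFR, and the analysis then reads lack of measurement as lack of recovery. CKD stage derived from that value inherits the error.

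Two things are at stake. The first is the level: each group's eGFR and CKD stage, and each patient's change, can be wrong without any comparison being made. The second is the before-versus-after contrast at Heartlands. There the after phase alone includes a follow-up clinic, so the intervention may alter how often and when creatinine is measured. The rule also gives every survivor a value. That hides how many patients have a usable later creatinine in routine records, which a feasibility study should report.

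**Working it through.** The plan states no figure for eGFR, so there is none to reproduce. The check is a logical one followed by illustrations.

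**1. What the rule does.** Each patient has at least one creatinine from the episode, the alert value. If a living patient has no later test, the last observation at day 90 is that value or another from the same episode, and it is the same at days 182 and 365. Nothing in the text prevents this.

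**2. Size for one patient.** Assumptions, none of them in the document: a man aged 70, baseline creatinine 100 µmol/L, the CKD-EPI 2009 equation, and full return to baseline.

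| Creatinine carried forward (µmol/L) | eGFR recorded | Understatement against 65.4 |
|---|---|---|
| 100 (baseline) | 65.4 | 0 |
| 150 (1.5 times) | 40.1 | 65.4 − 40.1 = 25.3 |
| 200 (2 times) | 28.3 | 65.4 − 28.3 = 37.1 |
| 300 (3 times) | 17.3 | 65.4 − 17.3 = 48.1 |

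The error is smaller if recovery is partial or if the carried value is a partly recovered discharge value. Nor is 25 a floor: Box 1 shows that a stage 1 alert can also arise from an absolute rise of 26 µmol/L.

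**3. Size for a group mean.** Let f be the share of survivors whose last value is from the episode, and D the mean shortfall of that value against true later eGFR. Then bias = −f × D. The document gives neither input. With f = 20% assumed, D = 10, 20 or 30 gives a bias of −2, −4 or −6 mL/min/1.73 m².

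**4. Before versus after at one site.** Spurious difference = (f before − f after) × D.

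- Equal shares, for example 20% and 20%: 0, although both levels stay biased.
- 30% before and 20% after: 0.10 × 10, 20 or 30 = 1, 2 or 3.
- Clinic affects stage 3 only. Let s be the share of survivors with stage 3 and u the gain in the share with a recovered later value. The overall difference is s × u × D, from 0.10 × 0.20 × 10 = 0.2 to 0.30 × 0.40 × 30 = 3.6. Within stage 3 it is u × D, from 0.20 × 10 = 2 to 0.40 × 30 = 12.

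All shares and shortfalls in steps 3 and 4 are assumptions. They show how the error works and are not estimates for this study.

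**The case against.** The strongest reply is that this is a feasibility pilot. eGFR is one of six secondary outcomes. The Statistical analysis section says that the study is not powered for a full before-and-after comparison, and it names dialysis use and non-dialytic complications as the safety indicators. The success criteria in the Discussion do not mention eGFR, and the 30-day composite is untouched. All of this stands and limits the severity. It does not excuse the rule, because the correction needs no recall.

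A reader might go further and infer that the intervention group is bound to look better, perhaps by 2.5 to 5 mL/min/1.73 m² (a 10-point gap in retesting times a shortfall of 25 to 48). The document does not support that:

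- The clinic is for stage 3 survivors only. The lower figure uses a 1.5-fold rise, which is not stage 3. The upper one needs an extra 10% of all patients to be newly tested stage 3 survivors.
- A visit about a week after discharge may come before recovery, so its creatinine may also be unrepresentative.
- Repeat creatinine is not among the listed diagnostic and monitoring items, and the Interventions section expects most patients to receive a single call.
- No retesting rates are given, and nothing in the article shows that recovered patients are tested less often.

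A reader might also infer that the analysis of end-stage renal disease is compromised. The article does not say that this is classified from a carried creatinine. Differences between the two sites in renal services do not bear on the planned comparisons either, since the article rules out comparing the sites directly.

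**Conclusion.** The point holds at moderate severity. It concerns a rule that the protocol article fixes, not a detail left to an analysis plan. As written, a survivor who is not retested has an in-episode creatinine recorded as long-term eGFR and CKD stage three times over. Provided that function recovers at least in part after the carried value, the error runs towards apparent CKD progression, in group levels and in individual change.

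For one illustrative patient the understatement is about 25 to 48 mL/min/1.73 m², on the assumptions of full recovery and a creatinine of 1.5 to 3 times baseline. The effect on group means depends on testing rates that the article does not give. A difference between phases at Heartlands is possible because of the clinic, but it could be negligible, and its size and direction cannot be determined from the document.

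**What to change.** Replace the carry-forward rule for eGFR as follows:

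1. At each of 90, 182 and 365 days, use only a creatinine taken within a prespecified window around that day, and never one from the index AKI episode. Define the end of that episode by a dated rule.
2. Treat living patients without such a value as missing.
3. Report the number and percentage with a measured value by group, phase and AKI stage, with deaths alongside.
4. Keep last observation carried forward only as a sensitivity analysis.
5. If a mixed model or multiple imputation is used, state that it relies on data missing at random. Add a sensitivity analysis in which testing depends on recovery, because neither method removes that bias.

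The cost is a change of wording and an extract from the laboratory data already in use, with no recall visits. The price is that fewer patients contribute a value, and those tested in routine care are a selected subset. The table of measured percentages makes this visible and is itself useful for planning the cluster trial.

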It was impractical to take written informed consent from the large numbers of patients involved over two hospitals, when the study was focused on providing AKI Outreach to clinicians. Therefore, it was agreed with the research ethics committee that we would write to all enrolled patients giving them an ‘opportunity to dissent’ or ‘opt out’ of the study. The opt out letter will be sent to the patient's home address as soon as possible after enrolment. In conjunction with the opt out letter, a leaflet explaining AKI will be sent to patients in the intervention group only.

The study is registered at ClinicalTrials.gov (NCT02398682). It is funded by the Research for Patient Benefit programme of the UK National Institute for Healthcare Research (PB-PG-1111-26038) and sponsored by the Heart of England Foundation Trust. The trial has two phases and four groups (2 during each phase—see also figure 1):
The before phaseDuring the 2-month before phase, patients in the two groups will be observed for the outcome measures, without any intervention, thus defining outcomes with good standard care. There will be two before phase groups:
Heartlands and area patients—patients with AKI in secondary and primary care—observed only.Good Hope and area patients—patients with AKI in secondary and primary care—observed only.The after phaseDuring the 5-month after phase, the intervention will be delivered to the intervention group (Heartlands and area) only. There will be two after phase groups:Heartlands hospital and area patients—intervention provided for patients with AKI in secondary and primary care, mainly using Outreach via telephone (see below).Good Hope hospital and area patients—patients with AKI in secondary and primary care—observed only.

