#### Alerts

The electronic AKI alerts are the trigger for the afferent arm of the intervention. The alerts are generated within the laboratory software (Telepath, Computer Sciences Corporation) according to the national algorithm.^25^ It compares the current patient creatinine to a value in the past (baseline creatinine). The staging follows KDIGO guidelines for AKI,^26^ where 0 is no AKI and 3 is the most severe stage. Alerts are made visible to all users of the electronic patient records, with the stage being stated as part of all urea, creatinine and electrolyte reports. The alerts from our hospital laboratory also contain a hyperlink to online guidance, with separate guidance for hospital and community alerts. Alerts are not issued for patients in the dialysis units and renal wards. We refer to the current location of the patient when discussing community (primary care) or hospital alerts. Obviously some of the hospital alerts will represent what was community-acquired AKI, but Outreach focuses on the current location of the patient.

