### Statistical analysis

The focus of the study is to assess feasibility of all aspects prior to full-scale evaluation. The data collected in this pilot study will be used to assess the uncertainty of the primary outcome. Further analyses will separately compare the before and after arms at the intervention and control sites. We note that the intervention and control sites cannot be directly compared. The control site data will be used to assess any ‘system-wide’ change in AKI outcomes. Additionally, survival analyses will be carried out, examining time to first composite primary outcome, and Kaplan-Meier survival curves produced for each of the four groups. This pilot study is not powered to provide a full comparison of the before and after phases. Among the end points, the use of dialysis and frequency of non-dialytic AKI complications will give an indication of the safety of the intervention. We will analyse estimated Glomerular Filtration Rate (eGFR) and CKD stage at a group level and changes at individual patient level. We will also explore the potential of using these data to validate our previous prognostic index.^9^

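### The complication indicator of safety cannot register events in patients who are never admitted, and takes two laboratory thresholds from the discharge letter

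*Protocol article*

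**What the plan says.** All references are to the protocol article.

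- **Source and window.** Under Outcomes, the secondary outcomes table lists key events with the index admission as their window. The text below it adds: "Key events are these events as given in the discharge letter". One of the two groups of key events is: "Complication of AKI not requiring dialysis: new pulmonary oedema, uraemia ≥30 mmol/L or hyperkalaemia (≥6.0 mmol/L".
- **Use.** Under Statistical analysis, "the use of dialysis and frequency of non-dialytic AKI complications will give an indication of the safety of the intervention".
- **Who is treated.** Under Overall study design, the Heartlands after-phase group is described as "intervention provided for patients with AKI in secondary and primary care, mainly using Outreach via telephone".
- **Some are not admitted.** Under Intervention package, the follow-up clinic for stage 3 survivors is timed "within 7 days of the alert if the patient is not admitted to hospital". The secondary outcomes table also counts "Percentage of patients admitted to hospital" within 14 days of the alert, so admission is an outcome and not an entry condition.
- **Laboratory data.** Under Alerts, the AKI stage is shown to users of the electronic record, "with the stage being stated as part of all urea, creatinine and electrolyte reports".

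**The concern.** The intervention covers hospital and community, but this safety measure is tied to an admission and its letter. The article names no other source for these complications. A community patient who develops potassium of 6.0 mmol/L or more and is managed without admission has no index admission in which the event could fall.

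Two of the three complications are numbers produced by a laboratory. Taking them from a letter makes the count depend on what its author chose to write.

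The Discussion and Conclusions make feasibility and safety the findings that would support a large cluster trial. The article also says that the secondary outcomes are collected here to test their feasibility for the main study, so an unrepaired definition could carry forward. The planned comparison is before against after within each site. A change in ascertainment confined to the Heartlands after phase would fall on the contrast of interest, and the control site would not show it.

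**Working it through.** The article gives no complication rate, admitted share or letter-recording rate, so there is no stated figure to reproduce. Its sample-size figures concern the composite outcome and do not enter here. The main check is a comparison of passages; the arithmetic only shows the mechanism.

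**Step 1: population against measure.** Treated population: hospital and community patients (Overall study design, Primary care sites). Measured population: those with an index admission and a discharge letter (Outcomes). The difference is the patients who are never admitted, whom the article foresees (Intervention package). That such patients have no relevant letter is inferred from the index-admission window.

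**Step 2: both possible denominators.** The article states none for key events.

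- *All patients:* those never admitted add to the denominator but cannot add to the numerator.
- *Admitted patients only:* the rate is coherent for that group but says nothing about the others.

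Either way, complications in non-admitted patients go undetected.

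**Step 3: dependence on admission, all-patient denominator only.** Let *a* be the admitted share, *r* the risk in admitted patients and *s* the share of events recorded in the letter.

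Recorded rate = a × r × s

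One pathway recommendation under Intervention package is to arrange outpatient review or admission for community patients, so *a* can change with Outreach. Assume r = 15% and s = 1, both constant:

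- a = 70%: 0.70 × 0.15 = 10.5%
- a = 80%: 0.80 × 0.15 = 12.0%, ratio 0.80 / 0.70 = 1.14
- a = 60%: 0.60 × 0.15 = 9.0%, ratio 0.60 / 0.70 = 0.86

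The ratio does not depend on *r*. The recorded rate moves in either direction with no change in the risk of admitted patients.

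**Step 4: how much might be missed.** Assume a risk of 15% in admitted and 3% in non-admitted patients.

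Share captured = (a × 0.15 × s) / (a × 0.15 + (1 − a) × 0.03)

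| a | s | True rate | Recorded rate | Captured |
|---|---|---|---|---|
| 90% | 100% | 13.8% | 13.5% | 98% |
| 80% | 80% | 12.6% | 9.6% | 76% |
| 70% | 80% | 11.4% | 8.4% | 74% |
| 60% | 60% | 10.2% | 5.4% | 53% |

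Across admitted shares of 60% to 90% and letter recording of 60% to 100%, capture runs from about 53% to 98%. All of these inputs are assumptions. With complete letters the admission restriction alone costs little at a = 90% (2% missed) and more at a = 60% (0.012 / 0.102 = 12% missed). The larger losses in the table come from the assumed letter recording.

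**Step 5: is another source available?** Of the three complications, urea of 30 mmol/L or more and potassium of 6.0 mmol/L or more are laboratory thresholds; pulmonary oedema is clinical. Urea and electrolyte reports come from the laboratory that issues the alerts, and the study portal sits within Trust IT (Data collection and recruitment). Practices using other laboratories generate no alerts for the study team (Primary care sites), so patients enrolled from primary care have at least their alert sample in the Trust laboratory.

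**The case against.** The strongest reply is that the index-admission window may simply confine this measure to admitted patients, with the denominator left to an analysis plan that is not shown. Death, dialysis and stage progression within 30 days, and later mortality, are not tied to a letter. The article claims only an indication of safety from a pilot that it says is not powered for a full before-and-after comparison. Laboratory ascertainment is imperfect too: patients are not recalled for renal function testing, and Outreach gives monitoring advice in the intervention arm only, so retesting may differ by group.

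These points limit the weight and shape the fix. They do not close the gap: an admitted-only denominator still leaves this indicator silent on non-admitted patients.

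Four stronger readings are tempting, and the article does not support them.

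- *Non-admitted patients are counted as event-free.* This holds only under an all-patient denominator, which is not stated.
- *Letters at Heartlands record more after an Outreach call.* This is plausible but not shown. The call goes to the clinical team, and nothing says that its recipient writes the letter.
- *More dialysis would hide harm by moving patients out of the non-dialytic count.* The counts are linked, but Statistical analysis already reads dialysis use beside them, so such a shift would appear there.
- *The study database already holds urea and potassium.* The article places these results in laboratory reports and does not say that the study database stores them.

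**Conclusion.** The point holds as a mismatch of coverage and source. One of the two named safety indicators is restricted to index admissions and discharge letters, while the intervention also reaches patients who may never be admitted. It cannot detect complications in them and, under an all-patient denominator, it also varies with an admission rate that Outreach can change. Two of its three components need not depend on a letter at all.

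The size cannot be determined from the article. The factors of 1.14 and 0.86 and the capture range of 53% to 98% follow from assumed rates and show only that the effect could be anything from negligible to substantial. Because this is a secondary outcome in a feasibility study and the other main outcomes do not rely on letters, the change is worth making but the weakness does not undermine the study as a whole.

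**What to change.** 1. Define urea of 30 mmol/L or more and potassium of 6.0 mmol/L or more from Trust laboratory results, for every patient in all four groups, admitted or not, within 30 days of the alert. That matches the primary outcome window.
2. Report values on the alert sample separately from later values. The alert sample precedes any Outreach contact and cannot reflect its safety.
3. Report each complication with and without dialysis, beside the dialysis counts already planned.
4. Report the proportion retested within 30 days, by group.
5. Keep the discharge letter for pulmonary oedema and the diagnoses, and state admitted patients as the denominator.

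**Cost.** A laboratory extract and a revised outcome definition, with no added visits or tests. The effort of the extract cannot be judged from the article. Ascertainment will still depend on how often patients are retested, which item 4 makes visible but does not remove. Later results processed by laboratories outside the Trust would also be missed.
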